This study will collect data from participating students in both study arms at three time points: pretest, posttest, and at a 3 months follow-up. All classes will be visited by project staff to administer the pretest. To ensure confidentiality, students will be spread out around the classroom and will be given privacy shields to block their computer or tablet screens from view. Secret ID numbers will be used in place of names on the questionnaires and will be sealed in envelopes between data collection time points. Students will be instructed that they can skip any questions they would like and that they may withdraw from the study at any time for any reason. Pretest questionnaires will be completed using computers or other Wi-Fi-enabled devices. Paper copies of the pretest questionnaire will be provided upon request or if technical problems with the online questionnaire occur. After pretest data collection is completed, teachers in the intervention group will have students who have permission to receive sexual health education complete *Media Aware* over the course of about one week (depending upon the school’s class schedule). It is anticipated that the program could be completed in four 45-min class periods. Teachers in the delayed-intervention schools will be asked to refrain from teaching sexual health or MLE until after the 3 months follow-up data collection. Project staff will return to all classrooms to administer the posttest questionnaire to students in the intervention group after completion of the *Media Aware* program (approximately four class periods), and to students in the delayed-intervention group approximately four class periods after their pretests have been completed. At posttest, participating students in the intervention group will also provide program feedback. After program implementation, teachers in the intervention group will provide feedback on their experiences. Project staff will return to the classrooms after approximately 3 months to administer the follow-up questionnaire. After the follow-up data are collected, teachers in the delayed-intervention group can use *Media Aware* with their students. Afterward, teachers in the delayed-intervention group will also be asked to provide feedback on their experiences implementing *Media Aware* with their students. There will be no special criteria for discontinuing or modifying allocated interventions. There is no anticipated harm.

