##### Student primary outcome measures

The primary outcome measures for students are the following:
*Sexual debut (8 items)*. Participants will be asked to indicate (1 = yes; 2 = no; 3 = unsure) their sexual experience including oral, vaginal, and anal sex (e.g., Have you ever had oral sex?). We will examine change in sexual activity between time points.*Contraception and protection use (2 items)*. Skip logic will be used. Participants who indicate sexual experience will be asked on a 3-point scale (1 = yes; 2 = no; 3 = unsure) about their contraception/protection use the last time they engaged in sexual activity (e.g., Did you use a condom the last time you had sex [anal or vaginal]?).*Willingness to engage in unprotected sex (1 item)*. Participants will be asked to indicate on a 4-point Likert scale (1 = very unwilling; 2 = unwilling; 3 = willing; 4 = very willing) how willing they are to engage in unprotected sex (i.e., Imagine you were with a boyfriend/girlfriend. They want to have sex, but neither of you have any form of protection. In this situation, how willing would you be to go ahead and have sex anyway?). This measure was adapted from Gibbons et al. [38].*Willingness to have sex (1 item)*. Participants will be asked to indicate on a 4-point Likert scale (1 = very unwilling; 2 = unwilling; 3 = willing; 4 = very willing) how willing they are to have sex in a relationship context. (i.e., Imagine you were with a boyfriend/girlfriend and they say they love you. They want to have sex. In this situation, how willing would you be to have sex?). This measure was adapted from Gibbons et al. [38].*Willingness to “hook up” against own wishes (1 item)*. Participants will be asked to indicate on a 4-point Likert scale (1 = very unwilling; 2 = unwilling; 3 = willing; 4 = very willing) how willing they are to “hook up” even if they are not sure that they really want to (i.e., Imagine you were with a boyfriend/girlfriend. They want to hook up, but you are not sure that you want to. In this situation, how willing would you be to go ahead and hook up anyway?). This measure was adapted from Scull et al. [34] and Gibbons et al. [38].*Intentions to engage in sexual activity with another person (4 items)*. Participants will be asked to indicate on a 4-point Likert scale (1 = not at all likely; 2 = unlikely; 3 = likely; 4 = extremely likely) how likely they are to engage in sexual activity in the next year (e.g., How likely is it that you will have any type of sexual contact with another person [oral sex, anal sex, vaginal sex, or genital-to-genital contact] in the next year?). This measure was adapted from L’Engle et al. [39], α = .77.*Intentions to use contraception/protection (3 items)*. Participants will be asked to indicate on a 4-point Likert scale (1 = not at all likely; 2 = unlikely; 3 = likely; 4 = extremely likely) how likely they are to use contraception (e.g., If you were to have vaginal or anal sex, how likely would you be to use a condom?). This measure was adapted from Jemmott and Jemmott [40].

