#### Outcome analyses

The immediate and short-term effectiveness of *Media Aware* for improving student outcomes will be examined using intention-to-treat analyses. Hierarchical linear modeling (with random intercepts at the school/teacher level) will likely be used to account for conditional nonindependence in outcome measures at posttest and follow-up using the SAS MIXED procedure and will examine multiple observations over time. An independent statistician will conduct interim analyses after all posttests are complete, and the PI and Co-Investigator (Co-I) will have access to the interim results. Given the minimal risk of the intervention, it is not anticipated that the trial will be terminated following these interim analyses. However, if the interim analyses suggest the possibility of any adverse effects of the trial on participants, the PI and Co-I will share the findings with the IRB chair and funder to determine how to proceed and whether or not the trial should be terminated. The PI and funder would make the final decision to terminate the trial, if necessary.

The model for the mean of each outcome will likely contain level 1 fixed effects representing the influence of (1) the student’s pretest score and (2) gender and level 2 fixed effects of condition. Student variables found to be nonequivalent between groups will be included as covariates in these models. The effect sizes will be calculated by dividing the appropriate contrast parameter by the sample standard deviation of the outcome. These analyses should reveal if there is a significant improvement in students’ sexual health and media outcomes after having received the program as compared with the delayed-intervention group. Follow-up analyses or structural equation modeling may be warranted. Qualitative analyses (media deconstruction skills) will be coded by research team members who will be blinded to intervention assignment. Unblinding will not occur.

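### The only model named is linear for the mean of each outcome, which does not suit two primary outcomes (sexual debut, contraception use) answered yes, no or unsure

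*Protocol article*

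**What the plan says.** Student primary outcome measures lists seven primary outcomes. Five are willingness or intention measures on 4-point Likert scales. The other two record behaviour:

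- **Sexual debut**, 8 items covering oral, vaginal and anal sex: "Participants will be asked to indicate (1 = yes; 2 = no; 3 = unsure) their sexual experience". The one analysis remark attached to it is "We will examine change in sexual activity between time points".
- **Contraception and protection use**, 2 items, under skip logic: "Participants who indicate sexual experience will be asked on a 3-point scale (1 = yes; 2 = no; 3 = unsure) about their contraception/protection use" at the last sexual activity.

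Outcome analyses names one model family: "Hierarchical linear modeling (with random intercepts at the school/teacher level) will likely be used to account for conditional nonindependence in outcome measures", in SAS MIXED, at posttest and follow-up. On scope it says: "The model for the mean of each outcome will likely contain level 1 fixed effects", namely pretest score and gender, with condition at level 2. Effect sizes are the contrast divided by the standard deviation of the outcome. Further analyses or structural equation modeling are left open. No categorical model is named and no outcome is exempted.

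On timing, Implementation procedure places the posttest of the delayed-intervention group "approximately four class periods after their pretests have been completed"; the intervention group is tested after completing the program, also about four class periods. The opening of the Discussion links behavioral effects to the 3 months after the program.

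**The concern.** The article states both the type of answer and the type of model, and for these two outcomes they do not fit. Yes, no and unsure are categories without an order, so a mean over them has no clear meaning until someone decides what is counted. The debut items ask whether something has ever happened. A student who has truthfully answered yes cannot become a new case on that item, yet a whole-sample model of the mean keeps that student in the contrast.

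At stake is the reading of the only behavioral primary outcomes. Depending on the coding, the contrast could mix behavior with uncertainty, or could understate an effect on debut. The investigators will also have access to interim results once posttests are complete, so the definition should not be left to be settled after that.

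**Working it through.** **Inputs.** From the article: answer codes 1, 2, 3 (Student primary outcome measures); linear mixed model for the mean (Outcome analyses); effect size 0.40, 100 students per school, ICC 0.05, α = 0.05, about 15 schools, 16 sought (Sample size and power calculation). The article gives no rates of yes or unsure, so every share below is an assumption.

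**1. The plan's own figure, as a yardstick.** The standard error of a standardised difference with J schools is √[(4/J) × (0.05 + 0.95/100)].
- J = 15: √(4/15 × 0.0595) = 0.126. Noncentrality is 0.40/0.126 = 3.18 on 13 degrees of freedom, and two-sided power is 0.835.
- J = 14: power is 0.804, so about 15 schools is consistent with the inputs.
- J = 16: the standard error is 0.122.

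The sample size is not in dispute; it only sets the scale for step 2.

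**2. If the printed codes were analysed.** Mean = 1·P(yes) + 2·P(no) + 3·P(unsure). Since P(no) = 1 − P(yes) − P(unsure), this equals 2 − P(yes) + P(unsure). The contrast is therefore the difference in P(unsure) minus the difference in P(yes).

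| Intervention yes/no/unsure (%) | Control yes/no/unsure (%) | Means | Difference in mean | Difference in P(yes) |
|---|---|---|---|---|
| 20/80/0 | 25/70/5 | 1.80 vs 1.80 | 0.00 | −5 points |
| 20/75/5 | 20/70/10 | 1.85 vs 1.90 | −0.05 | 0 |
| 25/69/6 | 25/73/2 | 1.81 vs 1.77 | +0.04 | 0 |
| 27/64/9 | 25/70/5 | 1.82 vs 1.80 | +0.02 | +2 points |

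The contrast can be zero when behavior differs and non-zero when it does not. In the last row it points towards less activity although more students report it.

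For scale, the variance is P(yes) + P(unsure) − [P(unsure) − P(yes)]².
- Row three: 0.274 and 0.217, a common SD of about 0.50, so 0.04/0.50 = 0.08 SD.
- Row four: 0.328 and 0.260, a common SD of about 0.54, so 0.02/0.54 = 0.04 SD.

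Both are below one standard error (0.12 SD).

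**3. If recoded to yes versus not yes.** The mean is P(yes) and the MIXED contrast is a risk difference, which can be interpreted. The planned effect size would still depend on prevalence. A 5-point difference is 0.05/√(0.10 × 0.90) = 0.17 SD at a rate of 10%, but 0.05/√(0.30 × 0.70) = 0.11 SD at 30%.

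**4. Lifetime items.** Let s be the share answering yes to the item at pretest. They cannot become new cases, so the whole-sample difference is s × 0 + (1 − s) × RD = (1 − s) × RD. For an illustrative RD of 5 points among students not yet experienced, s = 10% gives 4.5 points and s = 30% gives 3.5 points. Adjusting for pretest score does not undo this, because the model described has one condition effect common to all pretest levels.

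**5. Time point.** About four class periods separate pretest from posttest, so few debuts can fall between them. The Discussion's own window for behavior is the 3 months after the program.

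**6. Contraception use.** Only experienced students answer. Those who become experienced after pretest join the group later and have no pretest answer for the model to adjust for.

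**The case against.** The strongest case on the other side has five parts.

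- **The codes may never enter the model.** They are questionnaire response options, and the remark about change in sexual activity does not read like a comparison of mean codes. Scoring rules and the handling of unsure commonly sit in an analysis plan, which is not shown. This stands: a reader might infer that the contrast has no valid meaning, but the text does not support that, and the absence of a scoring rule is not in itself the fault. What remains is a mismatch between two things the article does state.
- **The model is only likely.** Both model sentences are hedged. That also stands, but the hedge offers no categorical alternative, and neither do the unspecified follow-up analyses.
- **A linear model on a recoded outcome is tolerable.** At the plan's ICC, the between-school share of a school mean's variance is 0.05/(0.05 + 0.95/100) = 84%, and the random intercept carries it. A reader might infer that the standard error would be badly wrong; these figures do not show that.
- **Dilution is not uniform.** The eight items cover different acts, so a student experienced in one can still be a new case on another. The factor (1 − s) therefore applies per item or per stated composite. A whole-sample risk difference is also a legitimate estimand, and moderator analyses by prior sexual experience are foreseen. Those would show the pattern but would not define the primary outcome as debut.
- **No posttest test of debut is promised.** The article speaks of posttest and follow-up for outcomes in general. The inference that half the debut tests are null by construction goes too far; a posttest contrast would be nearly uninformative.

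**Conclusion.** The point holds in a limited form. The one model named, a linear mixed model for the mean with effect size as contrast over SD, does not suit the two nominal primary outcomes, and these are the trial's only behavioral ones.

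The consequence depends on a coding choice that the article does not state. On the printed codes, the contrast would mix behavior with uncertainty, though under the assumed shares in rows three and four the distortion is only 0.04 to 0.08 SD, less than one standard error. After a yes/not-yes recode the contrast is a risk difference, and the remaining loss for debut is the factor (1 − s). That is a reduction of 10% to 30% if 10% to 30% of students are already experienced at pretest, a range the article does not give. The loss also assumes that students answer the lifetime items consistently over time.

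**What to change.** - **Debut:** define it, per act or as a stated composite, as a new yes at the 3-month follow-up among students who answered no to that item or composite at pretest.
- **Unsure:** state one rule, with a sensitivity analysis under the alternative rule. Setting unsure to missing discards observed answers that may depend on arm, so the choice needs a reason.
- **Model:** analyse debut and binary contraception use with a logistic mixed model, or another binary-outcome model, with a school random effect and small-sample degrees of freedom. Report a risk difference or an odds ratio. Keep MIXED for the scale outcomes.
- **Time point:** make 3 months the time point for the behavioral outcomes, in line with the Discussion.
- **Contraception use:** say that the contrast is among experienced students, a group formed partly after randomisation, and is to be read with that caution. The new model does not remove this limit.

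These rules should be fixed before anyone on the team sees results by arm. The cost is wording, on the same data. The downside is a smaller denominator for debut, although students already experienced on an item carry no information about debut on that item.

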
##### Student secondary outcome measures

The student secondary outcome measures are the following:
*Media message deconstruction skills (3 items)*. Participants will be shown an advertisement (Fig. 2) and asked to describe it in detail (e.g., How are advertisers trying to get someone to buy this product?). This measure was adapted from Kupersmidt et al. [41].*Message completeness (1 item)*. Participants will be shown the same advertisement and asked to indicate on a 4-point Likert scale (1 = incomplete to 4 = complete) how complete the information included in an advertisement is (i.e., How complete is the information in this advertisement?). This measure was adapted from Scull et al. [42].*Perceived realism of media messages (5 items)*. Participants will be asked to indicate on a 4-point Likert scale (1 = strongly disagree; 2 = disagree; 3 = agree; 4 = strongly agree) the degree to which they agree that media portray reality (e.g., Do teens in the media do things that average teens do?). This measure was adapted from Austin and Johnson [43], α = .75.*Perceived similarity to media messages (3 items)*. Participants will be asked to indicate on a 4-point Likert scale (1 = strongly disagree; 2 = disagree; 3 = agree; 4 = strongly agree) the degree to which they agree that media portrayals are similar to the participant’s own life (e.g., The things I do in my life are similar to what I see teens do in the media.). This measure was adapted from Austin and Johnson [43], α = .79.*Media skepticism (5 items)*. Participants will be asked to indicate on a 4-point Likert scale (1 = strongly disagree; 2 = disagree; 3 = agree; 4 = strongly agree) their level of agreement on several items pertaining to the media (e.g., Media are dishonest about what happens if people have sex.). This measure was adapted from Scull et al. [34], α = .86.*Acceptance of dating violence (4 items)*. Participants will be asked to indicate on a 4-point Likert scale (1 = strongly disagree; 2 = disagree; 3 = agree; 4 = strongly agree) their level of agreement on several items pertaining to dating violence (e.g., It is okay for people to hit their girlfriends/boyfriends if they did something to make them mad.). This measure was adapted from Foshee et al. [44], α = .78.*Acceptance of strict gender role stereotypes (6 items)*. Participants will be asked to indicate on a 4-point Likert scale (1 = strongly disagree; 2 = disagree; 3 = agree; 4 = strongly agree) their level of agreement on several items pertaining to strict gender role stereotypes (e.g., Raising children is primarily a woman’s responsibility.). This measure was adapted from Foshee et al. [44], α = .69.*Acceptance of rape myths (5 items)*. Participants will be asked to indicate on a 4-point Likert scale (1 = strongly disagree; 2 = disagree; 3 = agree; 4 = strongly agree) their level of agreement on several items pertaining to myths about rape (e.g., It shouldn’t be considered rape if a guy is drunk and didn’t realize what he was doing.). This measure was adapted from Payne et al. [45] and McMahon and Farmer [46]; the overall scale reliability was .87 and the subscales ranged from .64 to .80.*Efficacy to intervene as bystander (5 items)*. Participants will be asked to indicate on a scale of 0 (can’t do) to 100 (very certain) their level of confidence in several behaviors (e.g., I could talk to a friend who I suspected is in an abusive relationship.). This measure was adapted from Banyard et al. [47], α =87.*Intentions to intervene as bystander (4 items)*. Participants will be asked to indicate on a 4-point Likert scale (1 = not likely at all; 2 = unlikely; 3 = likely; 4 = extremely likely) how likely they would be to intervene as a bystander to prevent sexual or relationship violence (e.g., I would approach a friend if I thought they were in an abusive relationship and let them know that I am here to help.). This measure was adapted from Banyard et al. [47], α =94.*Sexual health knowledge (8 items)*. Participants will be asked several multiple choice and True/False questions about sexual health (e.g., True or False: Can you tell someone has an STI by looking at him/her? Answer: False). Some questions have more than one correct answer (e.g., Which of the following are methods of reducing the risk of pregnancy? Choose all that apply. Answer: male latex condom, birth control pill, birth control patch). Scores are a summation of correct answers; a higher score indicates a higher level of sexual health knowledge. Scores are calculated out of a possible 13 points. This measure was adapted from Scull et al. [34].*Descriptive norms: teen sexual activity (5 items)*. Participants will be asked to indicate what percentage (0% = no teens; 100% = all teens) of teens engage in sexual activity (e.g., oral sex, vaginal sex, anal sex). This measure was adapted from Scull et al. [34].*Descriptive norms: teen risky sexual activity (3 items)*. Participants will be asked to indicate what percentage (0% = no teens; 100% = all teens) of teens engage in risky sexual activities (e.g., What percentage of teens have sex with someone who is much older?). This measure was adapted from Scull et al. [34].*Descriptive norms: birth control (3 items)*. Participants will be asked to indicate what percentage (0% = no teens; 100% = all teens) of teens use contraception (e.g., What percentage of teens who have oral sex use a condom or a dental dam?). This measure was adapted from Scull et al. [34].*Descriptive norms: communication (3 items)*. Participants will be asked to indicate what percentage (0% = no teens; 100% = all teens) of teens communicate with parents, health providers, or another trusted adult (e.g., Before deciding to have sex, what percentage of teens talk with their boyfriend/girlfriend about sexual health?). This measure was adapted from Scull et al. [34].*Efficacy to use contraception/protection (4 items)*. Participants will be asked to indicate on a 4-point Likert scale (1 = strongly disagree; 2 = disagree; 3 = agree; 4 = strongly agree) how effectively they could get and use contraception (e.g., If I wanted to, I could get condoms or another form of contraception.). This measure was adapted from Soet et al. [48].*Efficacy to negotiate contraception/protection use (2 items)*. Participants will be asked to indicate on a 4-point Likert scale (1 = strongly disagree; 2 = disagree; 3 = agree; 4 = strongly agree) how effectively they could convince a partner to use contraception (e.g., If I decided to have sex, I could talk to any potential partner to make him/her understand why we should use condoms or other contraception.). This measure was adapted from Soet et al. [48].*Efficacy to communicate before sex (3 items)*. Participants will be asked to indicate on a 4-point Likert scale (1 = strongly disagree; 2 = disagree; 3 = agree; 4 = strongly agree) how effectively they could communicate with others about sexual health (e.g., I could talk with a boyfriend/girlfriend about using condoms for sexually transmitted infection protection.). This measure was adapted from Scull et al. [32].*Intent to communicate before sex (3 items)*. Participants will be asked to indicate on a 4-point Likert scale (1 = not at all likely; 2 = unlikely; 3 = likely; 4 = extremely likely) how likely they would be to communicate with others before sexual activity (e.g., Before deciding to have sex, how likely would you be to talk with your parents or another trusted adult about sexual health?). This measure was adapted from Scull et al. [32].*Communication frequency (3 items)*. Participants are asked on a 4-point Likert scale (1 = never; 2 = rarely; 3 = sometimes; 4 = often) about their frequency of sexual health communication with partners or trusted adults (e.g., How often do you talk with a doctor or other health professional?).
